## 12.2 Secondary outcome measures

### 12.21 Mental Health & Addictions support

Difference in time to access mental health & addiction services, where ***time to access is defined as the difference (hours) between the date of referral from the Case Manager to the date of the MH&A appointment.***

### 12.22 Healthcare utilization

Difference in incidence rates of healthcare days at 12-weeks from the start date of the TDTP, where ***healthcare days represent the number of days alive and registered for an emergency room, mental health outpatient or addictions outpatient visit, or admitted to an acute care, mental health or detoxification facility.*** The incidence rate is defined by the ratio of the total number of healthcare days relative to the total person days exposure over the 12-week TDTP. The potential number of healthcare days for each apprentice is the number of days alive during the 12-week TDTP, with the maximum being 84 days (=12 weeks x 7 days/week).

### 12.23 Apprentice Satisfaction

Difference in apprenticeship TDTP satisfaction scores, where ***TDTP satisfaction scores will be measured upon TDTP completion using the validated National Centre for Vocational Education Research Student Outcomes Survey Satisfaction scores.*** Since 1995, this survey has been used to measure student satisfaction with vocational education and training (21) (Appendix). The survey consists of 19 individual questions divided into 3 major themes (Teaching, Assessment, and Generic skills and learned experiences) and 1 summary question. The response for each question is a Likert scale from *Strongly disagree (score=0)* to *Not Applicable (score=5).* The mean score for each theme and the score for the summary question will be used to estimate the differences in TDTP satisfaction. Only apprentices who successfully complete the TDTP will be asked to complete the survey.

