#### 20.12c Apprentice satisfaction

We will use linear multivariate regression analysis to model the differences in mean scores for each domain (3 major themes and summary question) of the National Centre for Vocational Education Research Student Outcomes Satisfaction Survey. The interventions (Distress thermometer and MH&A) will be included as well as a variable for their interaction effect. We will also include time period (year-quarter) and an interaction term between the time period and each intervention (Distress thermometer and MH&A).

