# 35 Appendix

## 35.1 National Centre for Vocational Education Research Student Outcomes Survey

The responses to all questions are: Strongly disagree; disagree; neither; agree; Strongly agree; N/A

| **Teaching** |
| --- |
| My instructors had a thorough knowledge of the subject content |
| My instructors provided opportunities to ask questions |
| My instructors treated me with respect |
| My instructors understood my learning needs |
| My instructors communicated the subject content effectively |
| My instructors made the subject as interesting as possible |
| **Assessment** |
| I knew how I was going to be assessed |
| The way I was assessed was a fair test of my skills |
| I was assessed at appropriate intervals |
| I received useful feedback on my assessment |
| The assessment was a good test of what I was taught |
| **Generic skills and learning experiences** |
| My training developed my problem-solving skills |
| My training helped me develop my ability to work as a team member |
| My training improved my skills in written communication |
| My training helped me to develop the ability to plan my own work |
| As a result of my training, I feel more confident about tackling unfamiliar problems |
| My training has made me more confident about my ability to learn |
| As a result of my training, I am more positive about achieving my goals |
| My training has helped me think about new opportunities in life |
| **Overall satisfaction with the training** |
| Overall, I was satisfied with the quality of this training |

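### The satisfaction survey gives "Not Applicable" the highest score (5), so items that do not apply raise the mean satisfaction score

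*Protocol*

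**What the plan says.** Satisfaction with the training program is a secondary outcome (Section 1.1), with two comparative objectives attached to it (Section 7.2, objectives 3 and 7). Section 12.23 fixes its measurement:

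- **Scoring of an item.** The response "is a Likert scale from *Strongly disagree (score=0)* to *Not Applicable (score=5").
- **Structure.** "The survey consists of 19 individual questions divided into 3 major themes", with one further summary question.
- **Summary measure.** "The mean score for each theme and the score for the summary question will be used to estimate the differences in TDTP satisfaction".

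Appendix 35.1 gives the options in order: "Strongly disagree; disagree; neither; agree; Strongly agree; N/A".

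Section 20.12c gives the analysis: "We will use linear multivariate regression analysis to model the differences in mean scores for each domain (3 major themes and summary question").

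No section of the protocol sets N/A to missing or leaves it out of a theme mean.

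**The concern.** N/A says that an item does not apply to the respondent. It is not a degree of satisfaction and has no place on the agreement scale, let alone at its top. Under the stated rule, an apprentice who marks all six Teaching items N/A scores 5.00, while one who strongly agrees with all six scores 4.00. On the summary question, one N/A outscores every real answer.

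Two distortions follow. Where groups differ in how often items are inapplicable, the difference appears as a difference in satisfaction. Where they do not differ, every mean is inflated and a true difference shrinks.

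The comparison most exposed is that for the mental health and addictions service. The service is offered only at Barrie (Section 8), so any difference between the sites in N/A use falls directly on its estimated effect. Some use of N/A is plausible. The program is not formal education and 78% of its hours are hands-on site work (Section 5.15), yet the survey has five items on assessment and one on written communication.

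**Working it through.** **Inputs**

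- End points of the item score: Strongly disagree = 0, Not Applicable = 5 (Section 12.23).
- Six options in a fixed order, N/A last (Appendix 35.1).
- Items per theme, counted in Appendix 35.1: Teaching 6, Assessment 5, Generic skills 8. The sum is 6 + 5 + 8 = 19, as Section 12.23 states, plus one summary question.
- N/A rates and true group means are not in the protocol. Those used in steps 3 and 4 are assumptions.

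**Step 1: reproduce the scale.** Numbering the six options consecutively from 0 gives Strongly disagree 0, disagree 1, neither 2, agree 3, Strongly agree 4, N/A 5. Both stated end points are matched. The value 4 for Strongly agree is inferred, not printed, but the stated text alone already puts N/A at the top.

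**Step 2: effect on one respondent.** Let a theme have k items, of which m are marked N/A, and let b be the mean of the applicable items (at most 4).

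- Score as written: [(k − m)b + 5m] / k
- Score with N/A excluded: b
- Shift: (m/k)(5 − b), which is always positive because b cannot exceed 4

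Example: five Teaching items at 1 and one N/A give (5 × 1 + 5)/6 = 1.67, against 1.00 with N/A excluded.

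Shift from a single N/A, (5 − b)/k:

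| Theme | b = 4 | b = 3 | b = 2 | b = 0 |
| --- | --- | --- | --- | --- |
| Teaching (6) | 0.17 | 0.33 | 0.50 | 0.83 |
| Assessment (5) | 0.20 | 0.40 | 0.60 | 1.00 |
| Generic skills (8) | 0.125 | 0.25 | 0.375 | 0.625 |

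The shift is largest for the least satisfied respondents. With b = 4, one N/A lifts the theme mean above the best substantive score, to between 4.125 and 4.20.

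**Step 3: false difference between groups.** Suppose both groups have true mean μ, N/A use is unrelated to satisfaction, and the N/A rates differ by d. The false difference is d(5 − μ).

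| d | μ = 2 | μ = 3 | μ = 3.5 |
| --- | --- | --- | --- |
| 0.02 | 0.06 | 0.04 | 0.03 |
| 0.05 | 0.15 | 0.10 | 0.075 |
| 0.10 | 0.30 | 0.20 | 0.15 |
| 0.20 | 0.60 | 0.40 | 0.30 |

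**Step 4: equal N/A rates.** With rate q in both groups, a group mean becomes (1 − q)μ + 5q, so a true difference is multiplied by (1 − q). With q = 0.10 and true means 3.0 and 2.5, the reported means are 0.9 × 3.0 + 0.5 = 3.20 and 0.9 × 2.5 + 0.5 = 2.75. The true difference of 0.50 is reported as 0.45.

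**The case against.** The strongest reply concerns size. The protocol gives no N/A rate and no evidence that rates differ. Most items are generic enough to apply to almost any trainee, both sites run the same 12-week program, and only completers are surveyed. N/A may be rare, and a gap of 10 percentage points is large. This stands: differential use of N/A is possible, not shown to be likely, and the 0.20 is an illustration within the range in step 3.

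The site argument also has a limit. Cohorts are randomized to the distress tool within site, so site differences in N/A do not systematically bias the tool comparison. That would need the tool itself to change N/A use. The comparison for the mental health and addictions service is confounded with site whatever the scoring. This stands too. The scoring rule adds a further route for site differences into that comparison, and the shrinkage in step 4 applies to both comparisons.

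The score may be a slip for Strongly agree = 5, or the SAP, which is not shown, may set N/A to missing. A slip is possible, but five substantive options numbered consecutively from 0 would end at 4, whereas six end at 5, the value stated for N/A. Nor is this a detail left open for the SAP: the protocol assigns N/A a number, and an SAP that set it to missing would contradict the protocol.

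**Conclusion.** The point holds. Followed as written, Sections 12.23 and 20.12c make an inapplicable item the most favorable answer. The direction of the error is certain for any respondent who uses N/A. For an apprentice who otherwise agrees with every item (b = 3), one N/A adds 0.25 to 0.40 points to a theme mean, depending on the theme. The size at group level is unknown. Under assumed N/A gaps of 2 to 20 percentage points and true means of 2 to 3.5, the false difference runs from 0.03 to 0.60 points on a scale whose substantive range is 0 to 4.

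The damage is confined to one secondary outcome measured in completers. The text should be corrected before the score is programmed.

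**What to change.** In Section 12.23, score the five substantive options from 0 (Strongly disagree) to 4 (Strongly agree) and set N/A to missing. Define the theme mean over applicable items and state the minimum number required. At least half is a common convention (3 of 6, 3 of 5, 4 of 8), and another prespecified minimum would serve as well. An N/A on the summary question becomes missing. Report the frequency of N/A by group, so that a reader can see whether applicability differs between sites or arms.

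The survey is described as validated, but its published scoring is not reproduced in the protocol. Check the revised rule against that source before it is fixed.

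The cost is about one sentence in Section 12.23, one line of scoring code, and slightly fewer scored items. The model in Section 20.12c does not change.

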# 6 Hypotheses

## 6.1 Primary

In apprentices enrolled in the TDTP who are at-risk of absenteeism, drop-out or unemployment post-program completion, exposure to either the ICM^10^ or ICM^01^ models will be superior to the BCM model for reducing absenteeism (as determined by the number of absence-free days), drop-out (as determined by the proportion of apprentices completing the program), and unemployment (as determined by proportion employed at 24 months post-program completion).

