## 7.2 Secondary

1) To compare the effect ICM^10^ and ICM^01^ versus BCM on time to access mental health & addiction services

2) To compare the effect ICM^10^ and ICM^01^ versus BCM on utilization of healthcare visits

3) To compare the effect ICM^10^ and ICM^01^ versus BCM on National Centre for Vocational Education Research Student Outcomes Survey Satisfaction scores

4) To compare the effect ICM^10^ and ICM^01^ versus BCM on mean hours spent on case management by the Case Manager

5) To compare the effect of ICM^11^ versus ICM^10^ and ICM^01^ on time to access mental health & addiction services

6) To compare the effect of ICM^11^ versus ICM^10^ and ICM^01^ on utilization of healthcare visits

7) To compare the effect of ICM^11^ versus ICM^10^ and ICM^01^ on National Centre for Vocational Education Research Student Outcomes Survey Satisfaction scores

8) To compare the effect of ICM^11^ versus ICM^10^ and ICM^01^ on mean hours spent on case management by the Case Manager

9) To measure acceptability of using self-report tool for distress by apprentices and Case Manager

10) To measure feasibility of using self-report tool for distress by apprentices and Case Manager

11) To measure compliance of using self-report tool for distress by apprentices

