### 12.12 Program completion

Difference in proportion of drop-outs at 12 weeks from start date of TDTP, where ***a drop-out is defined as an apprentice who fulfils any of the following criteria:***

- Has missed more than 50% of training days, or
- Who has elected to leave the program for reasons other than taking another job or returning to school

The proportion of drop-outs is defined as the ratio between the cumulative number of apprentices who meet the criteria for drop-out relative to the cumulative number of apprentices enrolled in the TDTP.

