## 14.2 Difference in proportions of TDTP completion

Historical cohorts have demonstrated variation in program completion proportions but have been generally observed at a 75-80% graduation / completion rate. In this cluster randomized trial comparing the difference in proportions of TDTP completion, we define an *a priori* difference of ≥ 0.1 in completion proportions as the lower limit of a minimally significant difference (24). This is opinion-based on an informal survey of TDTP stakeholders. Given the same fixed sample and cohort size estimates discussed in Section 14.1, we performed a sensitivity analysis to determine the power to observe a difference in program completion proportions ≥ 0.1 using different control group completion rates with an $\alpha$-level 0.05**.**  As can be seen in the following table, a difference in completion proportions of 0.1 would be detected with power ≥ 80% as long as the control group completion proportion was ≥ 0.8, a reasonable assumption given the historically observed program completion proportions.

|  | **Scenarios**^1^ | | | | | | |
| --- | --- | --- | --- | --- | --- | --- | --- |
| **Variables** | 1 | 2 | 3 | 4 | 5 | 6 | 7 |
| Test Significance Level, α​ | 0.05 | 0.05 | 0.05 | 0.05 | 0.05 | 0.05 | 0.05 |
| 1 or 2-Sided Test?​ | Two | Two | Two | Two | Two | Two | Two |
| Control Group Proportion (p2)​ | 0.75 | 0.75 | 0.75 | 0.75 | 0.8 | 0.8 | 0.8 |
| Test Statistic under H0​ | 0 | 0 | 0 | 0 | 0 | 0 | 0 |
| Test Statistic under H1​ | 0.1 | 0.1 | 0.1 | 0.1 | 0.1 | 0.1 | 0.1 |
| Intracluster Correlation (ICC)​ | 0 | 0.05 | 0 | 0 | 0 | 0 | 0 |
| Clusters in Treatment Group (K1)​ | 20 | 20 | 33 | 25 | 20 | 33 | 25 |
| Clusters in Control Group (K2)​ | 20 | 20 | 33 | 25 | 20 | 33 | 25 |
| Cluster Ratio (K2/K1)​ | 1 | 1 | 1 | 1 | 1 | 1 | 1 |
| Cluster Sample Size in Treatment Group (M1)​ | 10 | 10 | 6 | 8 | 10 | 6 | 8 |
| Cluster Sample Size in Control Group (M2)​ | 10 | 10 | 6 | 8 | 10 | 6 | 8 |
| Cluster Sample Size Ratio (M2/M1)​ | 1 | 1 | 1 | 1 | 1 | 1 | 1 |
| Power (%)​ | 70.6 | 54.6 | 70.2 | 70.6 | 80.2 | 79.8 | 80.2 |

^1^ Highlighted cells (Yellow) represent changes from previous scenario

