All study-specific data that is survey-based (Section 18.13 and 18.13a) will be completed by apprentices during orientation or after the completion of the TDTP. Secure links for each of the surveys will be sent by email to each apprentice. All survey responses will be stored in REDCap using the previously assigned unique identifier. Study-specific data related to clinical outcomes will be extracted by study personnel from the electronic medical record system (dates and times of Mental Health and/or Addictions healthcare visits) and stored in REDCap. All other study-specific outcome data related to program completion and employment (Section 18.13) will be collected by study personnel who will enter the data in REDCap.

All study data will be archived in REDCap for 10 years and subsequently permanently destroyed.

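### Satisfaction is measured only in program completers, so its comparison between case-management models is made in groups selected after randomisation

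*Protocol*

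**What the plan says.** Section 12.23 measures satisfaction on completion of the TDTP with the vocational Student Outcomes Survey, and adds: "Only apprentices who successfully complete the TDTP will be asked to complete the survey". The timeline in Section 13 places the survey in the window after the program.

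Section 7.2 sets no such limit. Objective 3 compares ICM10 and ICM01 "versus BCM on National Centre for Vocational Education Research Student Outcomes Survey Satisfaction scores", and objective 7 repeats the comparison for ICM11 against ICM10 and ICM01. Section 20.12c fits a linear regression to the mean scores, with terms for both interventions, their interaction and time period. It does not mention apprentices without a score.

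Completion is a primary outcome (12.12), and the primary hypothesis (6.1) is that the ICM models reduce drop-out. A drop-out has missed more than half of the training days or is someone "Who has elected to leave the program for reasons other than taking another job or returning to school". Section 14.2 reports that past completion was "generally observed at a 75-80% graduation / completion rate" and sets a "difference of ≥ 0.1 in completion proportions as the lower limit of a minimally significant difference".

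Section 19 says: "Secure links for each of the surveys will be sent by email to each apprentice". Read alone, this might seem to cover leavers. It describes how surveys are delivered, however, and the same section has them completed at orientation or after the TDTP. The specific rule in 12.23 governs the satisfaction survey.

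**The concern.** Whether an apprentice has a satisfaction score depends on an event after randomisation that is itself a primary endpoint. If an intervention changes who completes, the scored apprentices in the two arms are no longer the groups that were randomised. The regression then answers how satisfied those who stayed were. The objectives ask whether the model changes satisfaction.

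Any difference in mean score would mix an effect on satisfaction with a change in who was retained. A later analysis plan cannot repair this by itself, because no leaver would have been asked. Any imputation for them would have no observed leaver score to inform it.

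**Working it through.** **Inputs from the protocol.** Control completion 0.75 to 0.80 and a difference of 0.10 (14.2); 400 apprentices (14.1), so about 200 per level of the self-report tool and about 100 per factorial cell if split evenly; two-sided alpha 0.05 (14.2). The protocol gives no figure for satisfaction, so every satisfaction gap below is an assumption.

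**The plan's own figure first.** Power for completion with n = 200 per group and ICC 0, taking p̄ as the mean of the two proportions:

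power = Φ{[0.10 − 1.96·√(2p̄(1−p̄)/n)] / √[(p₁(1−p₁) + p₂(1−p₂))/n]}

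- 0.75 v 0.85: (0.10 − 1.96 × 0.0400)/0.0397 = 0.544, power 70.7% (protocol: 70.6%).
- 0.80 v 0.90: (0.10 − 1.96 × 0.0357)/0.0354 = 0.849, power 80.2% (protocol: 80.2%).

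The completion rates used below are therefore the ones the protocol itself works with.

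**Who is not surveyed.** On these rates, 20-25% of control and 10-15% of intervention apprentices are never asked.

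**Share of intervention completers with no surveyed counterpart.** If the intervention only adds completers, the share is 0.10/p(intervention):

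- 0.10/0.85 = 11.8%
- 0.10/0.90 = 11.1%

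**Shift in the observed difference when the true effect on satisfaction is zero.** Let D be the number of SDs by which these added completers are less satisfied than the rest. Then shift = −D × share.

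| D (assumed) | 0.75 to 0.85 | 0.80 to 0.90 |
| --- | --- | --- |
| −0.5 (more satisfied) | +0.059 | +0.056 |
| 0 | 0 | 0 |
| 0.25 | −0.029 | −0.028 |
| 0.5 | −0.059 | −0.056 |
| 1.0 | −0.118 | −0.111 |

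**Second model as a check.** Let satisfaction have correlation r with a normal propensity to complete, and let the top fraction p complete. Then shift = r × [φ(z_t)/p_t − φ(z_c)/p_c], where subscripts t and c denote intervention and control and z is the cut-off that leaves the fraction p above it. The bracket is 0.2743 − 0.4237 = −0.149 for 0.75 to 0.85, and 0.1950 − 0.3500 = −0.155 for 0.80 to 0.90.

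- r = 0.3: about −0.045 to −0.047 SD
- r = 0.5: about −0.075 to −0.078 SD
- r = 0.7: about −0.105 to −0.109 SD
- r = −0.3: about +0.045 to +0.047 SD

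A simulation with 2,000,000 per arm and a true +0.20 SD benefit gave an observed +0.154 to +0.157 SD for r = 0.3 and +0.122 to +0.125 SD for r = 0.5.

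**Scale.** The smallest difference detectable with 80% power among completers, at ICC 0, is 2.8 × √(1/n_c + 1/n_t).

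- Pooled tool contrast: 2.8 × √(1/150 + 1/170) = 0.314 SD; 2.8 × √(1/160 + 1/180) = 0.304 SD.
- Cell contrasts, as the objectives are worded: 2.8 × √(1/75 + 1/85) = 0.444 SD; 2.8 × √(1/80 + 1/90) = 0.430 SD.

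For D from 0.25 to 1.0, the shift is about 9% to 38% of the pooled figure (0.0278/0.304 to 0.1176/0.314) and about 6% to 27% of the cell figure (0.0278/0.430 to 0.1176/0.444). A positive ICC would enlarge the detectable differences and reduce these shares.

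**The case against.** **Direction.** A reader might infer that the rule hides a benefit, because the intervention keeps marginal and less satisfied apprentices in the scored group. The documents do not support that. Sections 5.13 and 5.2 attribute non-completion to barriers such as mental health, substance use, family duties and transport, and to delayed access to care, not to dissatisfaction. The survey items (35.1) rate instructors, assessment and skills gained, not case management. An apprentice kept in the program by timely help could be as satisfied as the others, or more so. This objection stands.

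**The 0.10.** It is the smallest difference that stakeholders would regard as important, used for power. It is not a forecast. The 11-12% share also assumes that nobody leaves because of the intervention. If completion does not change and the same people stay, there is no bias. This stands too, and the calculation is conditional on it.

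**Content.** Some items presuppose substantial training. Leavers would answer after less exposure, which may itself differ by arm, and many may not reply. This has weight. It supports keeping an analysis of completers, but it does not turn that analysis into the effect the objectives ask for. Items on respect, opportunity to ask questions and feedback can be rated after a few weeks.

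**Scope.** MH&A is fixed by site (5.3, Section 8), so ICM01 versus BCM is Barrie versus Sudbury whoever is surveyed. The argument from randomisation applies to the self-report tool alone. Satisfaction is also one of several secondary outcomes, with no power claim attached.

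**Conclusion.** The point holds as a mismatch between objective and measurement. The objectives ask for an effect of the models on satisfaction, while the data are collected only in a group defined by a primary outcome. The loss of comparability follows from the text. The sign and size of any bias do not.

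On the protocol's completion rates, and with an assumed gap of 0.25-1.0 SD, the shift is about 0.03-0.12 SD. It goes against the intervention if the added completers are less satisfied and in its favour if they are more satisfied. That is modest, but not negligible beside detectable differences of 0.30-0.31 SD (pooled tool) or 0.43-0.44 SD (cells). The calculation rests on completion rising by 0.10, nobody being lost because of the intervention, and ICC 0. As the outcome is secondary and the remedy cheap, this is a change the sponsor should make, not one on which the trial depends.

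**What to change.** In 12.23, replace the completers-only sentence so that the survey link goes to every enrolled apprentice at 12 weeks from cohort start, or on leaving if earlier. Drop-outs under the missed-days rule have no leaving date, so the 12-week date applies to them. Align Sections 13 and 19 with this.

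In 20.12c, make the analysis of all enrolled apprentices by allocated model the main one, keep completers only as supportive, and report response by arm and completion status. Settle the scoring of the not-applicable answer at the same time: 12.23 gives it the top score of 5, and early leavers may choose it more often.

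If the sponsor prefers completers only, limit objectives 7.2(3) and 7.2(7) to completers and label the result as descriptive, not as an effect of the model.

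The cost is small: an emailed link to the 10-25% of apprentices who would otherwise not be asked. The budget (Section 34) already allows 400 hours for surveys at 1 hour each, which covers all 400. The downside is that some leavers will not reply and others will answer after less exposure, so selection is reduced and not abolished. The change does not remove the site confounding of the MH&A contrast.
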